## Abstract

**Background:**

A major barrier to successful treatment in alcohol dependence is psychiatric comorbidity. During treatment, the time to relapse is shorter, the drop-out rate is increased, and long-term alcohol consumption is greater for those with comorbid major depression or anxiety disorder than those with an alcohol use disorder with no comorbid mental disorder. The treatment of alcohol dependence and psychological disorders is often the responsibility of different services, and this can hinder the treatment process. Accordingly, there is a need for an effective integrated treatment for alcohol dependence and comorbid anxiety and/or depression.

**Methods/Design:**

We aim to assess the effectiveness of a specialized, integrated intervention for alcohol dependence with comorbid anxiety and/or mood disorder using a randomized design in an outpatient hospital setting. Following a three-week stabilization period (abstinence or significantly reduced consumption), participants will undergo complete formal assessment for anxiety and depression. Those patients with a diagnosis of an anxiety and/or depressive disorder will be randomized to either 1) integrated intervention (cognitive behavioral therapy) for alcohol, anxiety, and/or depression; or 2) usual counseling care for alcohol problems. Patients will then be followed up at weeks 12, 16, and 24. The primary outcome measure is alcohol consumption (total abstinence, time to lapse, and time to relapse). Secondary outcome measures include changes in alcohol dependence severity, depression, or anxiety symptoms and changes in clinician-rated severity of anxiety and depression.

**Discussion:**

The study findings will have potential implications for clinical practice by evaluating the implementation of specialized integrated treatment for comorbid anxiety and/or depression in an alcohol outpatient service.

**Trial registration:**

ClinicalTrials.gov Identifier: NCT01941693

## Background

There is a high rate of psychological comorbidity in people with alcohol dependence [1,2]. This is of concern given that, during treatment, the time to relapse is shorter, the drop-out rate is increased, and long-term alcohol consumption is greater for those with comorbid major depression or anxiety disorder than for those with an alcohol use disorder (AUD) with no comorbid mental disorder [3-5]. In the Australian National Survey of Mental Health and Wellbeing, Teesson and colleagues [6] reported that 33% of more than 10,000 respondents with an AUD also suffered from an anxiety or mood disorder as defined by the *Diagnostic and Statistical Manual of Mental Health Disorders,* 4th ed. (DSM-IV). In addition, this subpopulation was significantly more disabled and used health services more frequently than those with AUD with no comorbid mental disorder [6]. Results from the large alcohol treatment trial Project MATCH (Matching Alcohol Treatment to Client Heterogeneity) highlight psychiatric comorbidity as a significant factor influencing treatment response for alcohol dependence [7]. Similarly, we have reported that, among alcohol-dependent patients, clinically significant levels of depression predicted poor response to alcohol treatment [8]. Unfortunately, however, the treatment of alcohol dependence and psychological disorders is often the responsibility of different services, and this may hinder the treatment process. Accordingly, there is a need for an effective integrated treatment for alcohol dependence and comorbid anxiety or depression in outpatient services.

To date, research has usually assessed different psychosocial methods or pharmacological treatments targeted at alcohol dependence and psychological disorders separately. The focus has rarely been on concurrent treatment for both conditions. Regarding alcohol dependence and comorbid depression, there have been only two psychosocial intervention trials. Brown et al. [9] observed in 35 inpatients that adding CBT for depression versus relaxation training to standard partial hospital alcohol treatment was more effective in reducing depressive symptoms and some drinking outcomes than treatment for the alcohol problem only. They also observed that decreases in somatic depressive symptoms mediated the relationship between treatment condition and drinking outcomes. However, in a follow-up larger clinical trial, Brown et al. [10] found no significant differences on alcohol use outcomes and inconsistent effects on symptoms of depression. In both these studies, the interventions for depression and alcohol were not integrated, and the alcohol psychoeducational intervention was group-delivered only during the initial hospital stay.

There have been some studies investigating concurrent, but not integrated, treatments for alcohol dependence and anxiety disorders. Two studies found little beneficial effect from concurrent treatment for alcohol dependence and anxiety disorders (panic disorder and social phobia) [11,12]. However, in both studies, limited success may have been due, in part, to an inability to differentiate alcohol-related anxiety from non-alcohol–related symptoms at baseline assessment. Patients were either in withdrawal or not necessarily abstinent at the time of assessment, such that that anxiety symptoms resulting from alcohol withdrawal may have confounded the initial diagnoses. In many cases, symptoms of depression and anxiety resolve with abstinence so that further treatment is not required. However, in other cases where abstinence is achieved, these symptoms persist or worsen. To this degree, the stepped-care model entails assessing the outcome of primary treatment and systematically offering a secondary treatment where indicated and thus has the potential to provide a clearly structured, logical, and economical treatment [13-15].

One difficulty in devising integrated treatment for comorbid disorders is the limited research identifying reciprocal relationships between the disorders and the processes that may underlie these relationships. A number of processes have been proposed to underlie comorbidity between anxiety, depression, and alcohol dependence including 1) “self-medicating” a mood or anxiety disorder with alcohol [21,22], 2) the arousing and depressant properties of alcohol causing symptoms similar to anxiety and depression, and 3) trait-like factors such as anxiety sensitivity leading to poorly tolerated withdrawal [23,24]. Targeting specific mechanisms that may underlie comorbidity during treatment is likely to be a productive strategy.

We developed an integrated treatment for alcohol dependence and comorbid anxiety and/or mood disorder to be implemented and evaluated in an outpatient service-delivery setting. The specific aims of this study are 1) to assess the effectiveness of an integrated intervention compared with usual care at reducing alcohol consumption and anxiety and depression symptoms among alcohol-dependent patients with comorbid anxiety and/or depression in an outpatient hospital setting; 2) to determine factors that mediate the relationship between treatment condition and drinking and/or mood outcomes, and 3) to describe important factors relating to the maintenance of alcohol-related psychiatric comorbidity. This study design will draw on the stepped-care approach to interventions for alcohol dependence [14,15] and apply this approach to comorbid anxiety and depression by providing additional care for a second diagnosis when that diagnosis becomes clear. Hence, alcohol-dependent outpatients will undergo a stabilization period from alcohol followed by a formal assessment for diagnosis of anxiety and/or depression before being randomly allocated to receive either usual or integrated care.

## Methods

### Procedure

The flow of participants is outlined in Figure 1. The first phase of the study is to establish a stabilization period from alcohol for three weeks before entering the randomization step of the study. During the stabilization period, participants will have the option of pharmacotherapy using naltrexone (50 mg, 1 tablet daily), acamprosate (333 mg, 2 tablets 3 times daily, reduced to 4 per day for women weighing < 65 kg), or a combination of the two as medically prescribed based on physician judgment and participant preference. After a three- to four-week stabilization period, patients will undergo complete formal assessment for anxiety and depression. Those with a diagnosis of anxiety or depressive disorder, regardless of drinking outcome, will be offered the next step of care. The remaining participants will be monitored for a further nine weeks while receiving alcohol pharmacotherapy and/or usual counseling care. Patients to undergo the next phase will also continue to receive further alcohol pharmacotherapy as medically prescribed but will be randomized to one of two treatment groups: 1) integrated intervention for comorbid alcohol, anxiety, and/or depression, or 2) usual counseling care. Follow-up appointments will then be scheduled at weeks 12, 16, and 24 as described below.

**Figure 1 F1:**
[figure not shown]
Flowchart of participants through the trial.

### Participants

A total of 100 patients will be recruited from inpatients and outpatients of participating hospitals via flyers and community advertisements at local general practice offices, in newspapers, and on the Sydney Alcohol Treatment Group website. Conservatively assuming that 40% of respondents will not be eligible for randomization at step 2 following diagnosis for depression or anxiety disorder, we anticipate that 60 patients will be randomized to one of the two groups. Participant time and travel expenses will be reimbursed at follow-up assessments. The trial will be conducted at the Drug Health Services outpatient clinic of the Royal Prince Alfred Hospital, NSW, Australia. Ethics approval for the study has been granted by The Sydney Local Health District Ethics Review Committee (X05-0275).

### Randomization and allocation concealment

Randomization will be stratified according to concomitant selective serotonin reuptake inhibitor (SSRI) use and will by referring to the consecutively assigned subject identification number to a matched numbered envelope containing a random assignment card. Assessors will be blind to treatment allocation for the follow-up diagnostic interviews, and the same assessor will not assess the participant they assessed at baseline. Participants were asked not to mention their therapist or details of their therapy during their follow-up assessment. In order to evaluate the blinding process, assessors will be asked to which treatment group they believe each participant was allocated. A paper wall will be implemented whereby the researchers that obtain follow-up data will have no knowledge of treatment-group allocation.

### Step 1: inclusion and exclusion criteria for study enrollment

Inclusion criteria are as follows: alcohol dependence according to DSM-IV criteria, with alcohol as the subject’s drug of choice; age 18–65; adequate cognition and English-language skills to give valid consent and complete research interviews as assessed by the Mini Mental State Examination (MMSE); willingness to give written consent; abstinence from alcohol for between three and 21 days (standard clinical criteria for use of acamprosate or naltrexone); resolution of any clinically evident alcohol withdrawal as measured by the Clinical Institute Withdrawal Assessment for Alcohol–Revised (CIWA-Ar) [25]; and a positive score on the initial Comorbidity Suspicion Checklist (CSC). The CSC is a brief assessment to be administered at the first appointment. It is comprised of a one-page checklist to be filled in by one of the assessing clinicians to screen for current anxiety/depressive symptoms, previous diagnoses of comorbid conditions (anxiety disorder or depression), a previous history of treatment for comorbid conditions (anxiety disorder or depression), and a positive score on either the Mini Social Phobia Inventory (Mini-SPIN) for social anxiety [26] or the Kessler Psychological Distress Scale (K10) measure of psychological distress [27] for anxiety and depression.

Exclusion criteria include active major psychiatric disorder associated with significant suicide risk, pregnancy or lactation, advanced liver disease (hepatocellular failure, variceal bleeding, ascites, or encephalopathy), or other serious medical illness that would interfere with adherence to the study protocol.

### Step 2: inclusion and exclusion criteria for randomization

Inclusion criteria for randomization include abstinence and/or clinically significant reduction in alcohol use per clinician judgment, resolution of any clinically evident alcohol withdrawal as indicated by CIWA-Ar results, and case formulation and diagnosis for anxiety or depression. Exclusion criteria include alcohol consumption at baseline levels and resolution of clinically evident anxiety or depression as assessed by the case formulation (see below). These patients will be offered further treatment as appropriate within the service and will continue to be monitored.

### Instruments

#### Baseline assessment

Baseline assessment will be of 40 minutes’ duration and will be conducted upon consent to enter the trial. Data will be gathered on demographics, long-term alcohol consumption, medical history of alcohol- and nonalcohol-related illness, drug abuse, age of onset, and family history of alcohol problems. Recent (past 30-day) alcohol consumption will also be assessed by the timeline follow-back (TLFB) method [28]. Severity of dependence will be assessed by the Obsessive-Compulsive Drinking Scale (OCDS) [29] and by the Alcohol Dependence Scale (ADS) [30]. Functional disability will be assessed by the Short-Form Health Survey (SF-12) [31]. Depression, anxiety, and stress levels will be measured by the Depression Anxiety Stress Scales (DASS) [32]. Motivation to change and perceived self-efficacy are likely to vary between individuals and be a determinant of treatment outcome; therefore, these will be assessed by the Stages of Change Readiness and Treatment Eagerness (SOCRATES) Scale [33] and the Alcohol Abstinence Self-Efficacy (AASE) Scale [34]. Sleep disturbance will be assessed by the Insomnia Severity Index (ISI) [35], and the psychological basis of insomnia will be assessed by the Glasgow Sleep Effort (GSES) Scale. History of other drug use will be determined by the Opiate Treatment Index (OTI) interviewer-conducted questionnaire. Blood samples will be taken for full blood count and liver function tests.

#### Formal diagnosis of comorbid anxiety or depression (stepped-care assessment)

Several additional indices will be assessed at the commencement of the stepped-care phase:

•*Interview measures:* Recent (past 30-day) alcohol consumption will be available from the drinking diary cards offered upon entry to the trial. Diagnoses of anxiety and affective disorders will be established by the Anxiety Disorders Interview Schedule (ADIS) for DSM-IV [36]. The structured interview for the Hamilton Rating Scale for Depression (HRSD) will be used to measure the severity of depressive disorders [37]. The International Personality Disorder Examination [38] will be used to screen for personality disorders.

•*Questionnaire measures:* Continuous measures of change for anxiety or depression will be obtained by administering the DASS [32]. Recent severity of alcohol dependence will be assessed by the OCDS and by the ADS [30]. Functional disability will be assessed by the SF-12 [31]. Information from all sources will be integrated into a case formulation following methods described by Persons and Tompkins [39].

#### Follow-up schedule and assessments

Brief reviews will be scheduled with clinic medical staff at weeks 1, 6, 12, 16, and 24. Clinical and psychosocial events related to alcohol will be recorded along with serial liver function tests and mean corpuscular volume at baseline and at 6, 12, 16, and 24 weeks. At weeks 12, 16, and 24, the following research instruments will be administered as described above: DASS, ADS, SF-12, OCDS, GSES, ISI, AASE, SOCRATES, OTI, and a TLFB. At week 16, sections of diagnostic interviews relevant to diagnoses established at randomization (entry to step 2) will be readministered by a blind assessor. Recent alcohol consumption will be assessed as above and with a daily diary. Throughout the trial, any adverse and serious adverse events will be recorded. Participants will provide information concerning at least two contacts and receive three attempts at telephone or mail reminders of forthcoming appointments.

### Intervention

#### Usual care

Counseling for the treatment of alcohol dependence will continue in accordance with standard practice at the participating treatment site [40]. This entails brief individualized motivation enhancement therapy (ie, feedback of assessment findings, reinforcement, empathy, enhancing client’s own motivation). Participation in treatment sessions will be recorded. As quality-control measures, counselors will be supervised by senior staff and engage in weekly meetings, and treatment will be delivered according to the evidence-based treatment manual of Jarvis et al. [40].

#### Intervention for alcohol and comorbid anxiety and/or mood disorder

Structured interviews will be audiotaped and reviewed by the clinical team to develop consensus case formulations. Trained therapists will deliver specific CBT interventions based on evidence-based treatment manuals for alcohol use, anxiety, and depressive disorders (Table 1). Cognitive restructuring and graded exposure or behavioral experiments are techniques that are common to CBT for most of these individual disorders. Cognitive restructuring involves helping patients identify the key beliefs they hold about themselves, the future, the outside world, and other people that maintain their drinking, anxiety, or depression and assisting them to dispute and develop more helpful alternative beliefs. Graded exposure and behavioral experiments involve the gradual and programmed confronting of feared situations and has been argued to be the single most successful technique for overcoming phobias. These are necessarily brief descriptions for therapy that are well-documented in the treatment manuals displayed in Table 1. These manuals will be adapted for use with an alcohol-dependent population, and cognitive-behavioral coping skills and motivational enhancement strategies for alcohol consumption will be used where appropriate [41,42]. We expect different and complex interactions between the comorbid disorders, because the patients targeted for this study will experience significant comorbidity. An individualized case formulation, which hypothesizes the factors that maintain each individual’s problems, will be constructed following assessment using standard methods [39] (Table 2). The interventions will be delivered in seven to 10 sessions. To ensure that therapists adopt and maintain the principles of the therapy as described in the manual, sessions with consenting subjects will be audiotaped for discussion with the therapist early in the study (n = 4 per therapist) and at random times later in the study (n = 4 per therapist).

**Table 1 T1:** Cognitive behavioral therapy manuals forming the basis of integrated care for depression, anxiety, and alcohol use disorders

**Diagnosis**	**Manual**
Depression	Persons et al. [43]
Social phobia	Rapee [44] Rapee & Sanderson [45]
Panic disorder or agoraphobia	Andrews et al. [46]
Generalized anxiety disorder	Andrews et al. [47]
Post-traumatic stress disorder	Foa & Rothbaum [48], Najavits [49]
Alcohol use disorders	Monti et al. [41] Miller et al. [42]

**Table 2 T2:** Schedule of assessments

**Measure**	**Schedule**
Mini Social Phobia Inventory (Mini-SPIN)	Intake screening
Kessler Psychological Distress Scale (K10)	Intake screening
Comorbidity Suspicion Checklist (CSC)	Baseline (step 1*)
DSM-IV assessed dependence	Baseline (step 1)
Alcohol Dependence Scale (ADS)	Baseline (step 1), Weeks 12, 16, 24
Obsessive Compulsive Drinking Scale (OCDS)	Baseline (step 1), Weeks 12, 16, 24
Stages of Change Readiness and Treatment Eagerness (SOCRATES) Scale	Baseline (step 1), Weeks 12, 16, 24
Alcohol Abstinence Self-Efficacy (AASE)	Baseline (step 1), Week 12, 16, 24
Short-Form Health Survey (SF-12)	Baseline (step 1), Week 12, 16, 24
Depression Anxiety Stress Scale (DASS)	Baseline, Week 3 (step 2**), 12, 16, 24
Insomnia Severity Index (ISI)	Baseline, Week 3 (step 2), 12, 16, 24
Glasgow Sleep Effort Scale (GSES)	Baseline, Week 3 (step 2), 12, 16, 24
Timeline Follow-back (TLFB)	Baseline, Week 3 (step 2), 12, 16, 24
Anxiety Disorders Interview Schedule (ADIS)	Week 3 (step 2), Week 16
Hamilton Rating Scale for Depression (HRSD)	Week 3 (step 2), Week 16

*Step 1 = week 0 preceding three-week alcohol stabilization phase.

**Step 2 = formal diagnosis for depression and/or anxiety disorder preceding randomization to usual care or integrated care.

### Outcome measures

Primary outcomes include time to consumption of any alcohol (lapse) as identified by self-reported alcohol consumption; time to relapse as ≥ 4 drinks for women, ≥ 6 drinks for men; amount of alcohol consumed (total abstinence and average consumption per drinking day). Secondary outcomes include improvement in depressive or anxiety symptoms (DASS) or alcohol dependence severity (ADS); biological markers of alcohol consumption at 6, 12, 16, and 24 weeks (carbohydrate-deficient transferrin, liver function, and mean corpuscular volume); episodes of alcohol-related harm (psychosocial, occupational, forensic, medical); and clinician-rated severity of anxiety and depression based on ADIS and HRSD.

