### Statistical analysis

The modified intention-to-treat principle will be used such that all subjects who attend the first intervention session will be analyzed [50]. The success of randomization will be tested by comparing baseline characteristics of the study groups with potentially confounding variables included as covariables. Analysis of variance will be used to compare continuous variables. Categorical variables will be compared via chi-square test. The effect of treatment on time-related outcome measures such as lapse and relapse will be analyzed by life-table survival analysis. Binary linear generalized estimating equations (GEE), with autoregressive correlation matrices, will be employed to determine differences between integrated care and usual care groups on change in anxiety or mood symptoms. A series of regression analyses will be performed to assess the role of symptomatic change in alcohol consumption and vice versa. Last-point carried forward or multiple imputation will be used to determine the scores of participants who drop out or are lost to follow-up. One previous study [9] with a similar design (N = 35) demonstrated that combined CBT treatment of alcohol dependence and comorbid depression significantly improved alcohol use outcomes with a moderate effect size. Power analysis has thus been performed such that a sample of 60 subjects (30 per group) has 80% power of detecting a moderate difference between the two arms of care on alcohol use outcomes at alpha = 0.05.

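### The abstract names three primary drinking outcomes and the Methods four; none is singled out as decisive, and a single alpha of 0.05 is attached to them collectively

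*Protocol article*

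**What the plan says.** The abstract of the protocol article (Methods/Design) states: "The primary outcome measure is alcohol consumption (total abstinence, time to lapse, and time to relapse". That is one construct with three components.

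The Outcome measures section uses the plural and begins: "Primary outcomes include time to consumption of any alcohol (lapse) as identified by self-reported alcohol consumption". It continues with "time to relapse as ≥ 4 drinks for women, ≥ 6 drinks for men" and then "amount of alcohol consumed (total abstinence and average consumption per drinking day". That makes four measures, and average consumption per drinking day is the one that the abstract does not have. The section ranks none of them. The only assessment weeks it gives belong to the biological markers, which are secondary.

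On timing, the Procedure section says: "Follow-up appointments will then be scheduled at weeks 12, 16, and 24 as described below". No visit is named as primary for either amount measure.

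The Statistical analysis section assigns methods by type of variable: life-table survival analysis for lapse and relapse, chi-square for categorical variables and analysis of variance for continuous ones. It claims "80% power of detecting a moderate difference between the two arms of care on alcohol use outcomes at alpha = 0.05" with 60 participants, 30 per group.

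**The concern.** The two lists cannot both be the primary outcome of the same trial. A reader of the final report could not tell from this article whether average consumption per drinking day was meant to carry the primary claim.

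Beyond the mismatch, nothing identifies the result on which the trial stands or falls. The outcomes call for different tests, and the single 5% level in the power statement is attached to the whole group. At stake are the error rate behind any primary claim, and protection against the deciding outcome, or the visit for the amount measures, being settled after the data are known.

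**Working it through.** **Inputs from the protocol article**
- Primary outcomes: 3 in the abstract, 4 in Outcome measures.
- 30 versus 30 participants, 80% power, alpha 0.05 (Statistical analysis). Sidedness is not stated and is taken as two-sided.
- Research visits at weeks 12, 16 and 24.

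**Assumptions (not in the documents)**
- 60-85% of participants lapse by week 24.
- Relapse falls on the same day as the lapse in 35-80% of lapsers and later in the rest.
- Outcomes within a person are correlated through a shared severity term.
- A significant result on any one primary outcome counts as success.

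**1. The plan's own figure.** It cannot be reproduced, because the moderate difference has no number. Working backwards for a comparison of two means, the standardized difference detectable with 80% power is (1.960 + 0.842) × √(2/30) = 2.802 × 0.2582 = 0.72. That holds for one test at 0.05.

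**2. Independent tests.** The chance of at least one p < 0.05 under no effect is 1 − 0.95^k.
- k = 3: 1 − 0.8574 = 14.3%.
- k = 4: 1 − 0.8145 = 18.5%.

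The drinking outcomes overlap, so for these numbers of tests the true rates should be lower.

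**3. Equally correlated normal test statistics (400,000 draws).**

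| Correlation | 3 tests | 4 tests |
|---|---|---|
| 0.5 | 12.6% | 15.5% |
| 0.8 | 9.8% | 11.4% |
| 0.9 | 8.3% | 9.4% |

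**4. Patient-level simulation under no effect.** Trials of 30 versus 30, with log-rank tests for lapse and relapse, chi-square for abstinence over the whole period and a t-test for drinks per drinking day. Two versions were run with different assumptions.

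| Version | Lapse by week 24 | Abstract's 3 | Methods' 4, one visit |
|---|---|---|---|
| A (4,000 trials per setting) | 60 / 75 / 85% | 8.0-9.7% | 12.5 / 13.0 / 14.1% |
| B (3,000 trials per setting), same-day relapse 50% | 60% | 8.3% | 12.9% |
| B, same-day relapse 50% | 80% | 10.3% | 14.9% |
| B, same-day relapse 80% | 80% | 8.5% | 13.2% |

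The simulation error in version B at 13% is about √(0.13 × 0.87 / 3,000) = 0.6 percentage points. In version B each test taken alone rejected in 4.5-5.6% of trials, so the excess comes from having several tests.

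**5. If amount were also tested at several visits.** Repeating only average consumption at the three visits (6 tests) gives 18-20%. Repeating both amount measures (8 tests) gives 24-25%. The article does not say that this will be done.

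**6. Keeping all four with an equal split of alpha.** Each test has 0.05/4 = 0.0125. The detectable difference rises to (2.498 + 0.842) × 0.2582 = 0.86. Power at 0.72 falls to Φ(2.802 − 2.498) = Φ(0.304) = 62%. This applies to a comparison of means only.

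**7. Why power must be redone if a time-to-event outcome is chosen.** Events needed at 80% power are 4 × 2.802² / (ln HR)² = 31.4 / (ln HR)². For assumed hazard ratios of 0.40, 0.45 and 0.50 this gives 38, 50 and 66 events. The last figure exceeds the 60 participants.

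**The case against.** The strongest reply is that this is a journal article and the full protocol and analysis plan are not shown. A testing order, an alpha split or another multiplicity rule may be there, so their absence here is no finding. That stands. It does not reach the mismatch: the article states the primary outcome twice and differently, and no other document can make both statements true. Abstract shortening may explain the missing item, but the two lists still have to be reconciled.

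It is also fair that no passage says success on any one outcome suffices. The error rates are conditional on that reading and on lapse rates and correlations that the article does not give.

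Four stronger readings are tempting but not supported:
- A reader might multiply four outcomes by three visits and count 12 tests. Lapse and relapse are one survival analysis each, and the Statistical analysis section does not say that amount is tested visit by visit.
- A reader might say that total abstinence and time to lapse are the same event tested twice. Outcome measures gives no window for abstinence, so this is not established. If it were so, the overlap would lower the inflation, and the simulations in step 4 already assume it.
- A reader might see a conflict with the aim stated in the Background, "at reducing alcohol consumption and anxiety and depression symptoms among alcohol-dependent patients with comorbid anxiety and/or depression". A broad aim does not contradict a ranking, and the abstract and Outcome measures agree that symptoms are secondary.
- A reader might take the power statement as a promise of a 5% trial-wide error rate. It gives only the level used for the power calculation.

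**Conclusion.** The concern holds in this form. The article contradicts itself on whether there are three or four primary drinking outcomes, singles out none, gives no primary time point for the amount measures, and states power for "between the two arms of care on alcohol use outcomes at alpha = 0.05". Confidence in this is high, because it rests on the text alone.

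The size is less certain. If any one success counts, the false-positive chance is about 8-10% for three outcomes and 12-15% for four, roughly two to three times the nominal 5%. It would be higher if amount were also tested at several visits. Every setting tried exceeded 5%, including a pairwise correlation of 0.9. The article does not show that the trial will be analysed in this way; it only fails to exclude it.

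**What to change.** - Make the primary outcome identical in the abstract and in Outcome measures.
- Name one primary outcome with one time window. Time to relapse is an example, since it is in both lists. It would need its start point stated, because the Step 2 criteria admit participants who have reduced drinking without abstinence. It would also need the time unit to which its drink thresholds apply.
- Tie alpha = 0.05 and the power statement to that outcome, with a numerical effect size and a calculation suited to its type (events, if it is a time-to-event outcome).
- Make the other drinking outcomes secondary, with a single amount contrast at one visit or averaged over follow-up. If total abstinence covers the same window as time to lapse, keep only one of the two in any ordered set.

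With one named test, the chance of a false primary result returns to 5%. The cost is revised wording, one power calculation and a check that the registry entry agrees; no additional participants are needed to name the outcome. The downside is that the remaining drinking outcomes lose primary status, and the recomputed power may prove lower than 80%. The change should be made before any outcome data are seen by arm.
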